### **1.2.7 Recruitment**

The villages were randomly selected by a UK statistician from a list of all villages in CRR after applying the selection criteria. We provided written and oral information and received informed consent from the village heads for the participation of the villagers in the programme.

For the baseline and evaluation surveys, a list of all mothers with children between 6-24 months of age living in the village at the time was obtained from the maternal-child health register, and households were chosen randomly based on the study criteria. Mothers gave written informed consent. In case where the mother was illiterate, the information was read out (and a written copy left behind), and a thumb print obtained in the presence of a family witness and the data collector.

### **1.2.8 Baseline measurement**

During the initial recruitment visit to the head of village (December 2014; dry season), after receiving consent, we characterised all 30 villages before randomisation. We also collected data on 20 randomly chosen mothers for the baseline survey.

### **1.2.9 Randomisation**

Randomisation was conducted by a statistician in the UK: the villages were grouped and randomised within strata (north or south of the river, and by quartiles of the population size of the village) into 15 control and 15 intervention villages.

### **1.2.10 Blinding**

Blinding of the implementers of the intervention programme and of families who received the intervention was not possible. However, the families were not aware of the comparative nature of the intervention with a control village. The independent data collectors at evaluation were newly recruited as assessors, and the weaning-food hygiene evaluation items were concealed in a package of household observation tools and questionnaires about food and water use. Furthermore, the assessors and mothers were told that the evaluation investigated domestic water and food usage. As such they were not aware of the intervention or control nature of the evaluation. The laboratory technicians were blinded, as the samples were labelled with codes.

#### **1.2.11 Analysis of evaluation data**

The outcome analysis will be by intention-to-treat, however, missing data will be reported and associations between outcomes explored. Mixed models will be used to adjust for clustering. The outcomes are either binary (e.g. diarrhoea in the last seven days), continuous (e.g. the total coliform counts), or count (5-behaviours). The primary outcome (5-behaviours) will be analysed using a mixed effect Poisson regression model, with the number of completed behaviours as the outcome, and an offset for the number of opportunities to exhibit the behaviour. For all secondary outcomes, we will use a mixed effect linear regression model for continuous outcomes, and a Poisson mixed effect model with a log link for binary outcomes. All models will contain robust standard errors to allow for the misspecification of the variance. Data will be transformed, where necessary, if the transformation will improve the model. We will consider the comparisons to be significant at the 5% level (report 95% CIs).

For all outcomes, the primary analysis will be unadjusted for all covariates other than cluster and those covariates used in the stratified randomisation procedure (i.e. north / south of river

and village size). The secondary analysis will also adjust for a set of pre-specified and clinically important covariates (age and education of mother, parity, sex of child, order of intervention implementation, and other intermediate outcomes where health outcomes are concerned).

Where available, baseline data will be inserted as a co-variate in the analysis. All analyses will be conducted using Stata 15.

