### **1.2.6 Sample size**

Observations during the formative research indicated that the population proportion of events in which correct behaviour was displayed (i.e. practices of heating of stored food, hand washing with soap before food preparation, during food preparation if contaminated, and before feeding the baby (measured in the first time activity occurred)) was 17/150 (11.3%). For the sample size calculation, we assumed an intra-cluster correlation coefficient (ICC) of 0.04 between villages and a coefficient variation of cluster size 0.22. We aimed to detect a minimum of a 25% absolute increase in behaviour in the intervention compared to the control arm. Thus with a significance level of 5% and 95% power, 15 clusters per arm, with a

minimum of 12 mothers per cluster was needed. Assuming loss to follow-up we intended to recruit 20 mothers within each village. In a sensitivity analysis, assuming a larger ICC of 0.1, the power (84%) remained reasonable.

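### Robust standard errors on 30 villages with no stated small-sample correction: if run with the usual normal reference, the 5% tests operate at about 7-10%

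*Protocol*

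**What the plan says.** Protocol section 1.2.9 allocates the villages "into 15 control and 15 intervention villages", within strata defined as "north or south of the river, and by quartiles of the population size of the village".

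Section 1.2.11 sets the analysis:

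- Clustering: "Mixed models will be used to adjust for clustering".
- Primary outcome: "The primary outcome (5-behaviours) will be analysed using a mixed effect Poisson regression model", with an offset for opportunities. Binary outcomes also get a mixed Poisson model and continuous outcomes a mixed linear model.
- Variance: "All models will contain robust standard errors to allow for the misspecification of the variance".
- Primary-analysis covariates: besides cluster, "those covariates used in the stratified randomisation procedure", that is river side and village size.
- Level: "We will consider the comparisons to be significant at the 5% level (report 95% CIs".

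The section does not say whether tests refer to a normal or a t distribution, how many degrees of freedom apply, or whether the sandwich variance is corrected for few clusters. No permutation test or village-level analysis is mentioned. Section 2.1.5 applies this plan to the 2-year data.

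**The concern.** The sandwich variance is justified as the number of clusters grows. The cluster here is the village, and there are 30. More mothers per village (23-26 at 2 years, section 2.1.3) do not help. The primary model also spends village-level degrees of freedom on arm, river side and size, all of which vary only between villages. The residuals that feed the sandwich are then too small on average, so the standard error is biased downwards. A normal reference adds a second error, because it treats that standard error as known.

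At stake is whether the stated 5% level and 95% coverage are delivered, for the primary outcome and for every secondary outcome analysed the same way.

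**Working it through.** **Inputs from the protocol.** 30 villages, 15 per arm (1.2.9). River side and village size in the primary model (1.2.11). ICC 0.04, sensitivity value 0.1, cluster-size CV 0.22 (1.2.6). Nominal level 5%.

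**Inputs assumed, not in the protocol.** Normal reference; cluster sandwich with only the factor J/(J-1), J = 30; about 5 or 10 opportunities per mother; within-mother correlation 0.2; outcome proportions 0.113 to 0.35.

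**Step 1: village-level degrees of freedom.** With p village-level parameters, df = 30 - p.

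- Intercept and arm only: p = 2, df = 28.
- Plus river side and linear size: p = 4, df = 26.
- Plus river side and size quartiles (three indicators): p = 6, df = 24.

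**Step 2: normal reference alone.** P(|t| > 1.96) is 6.0% at 28 df, 6.1% at 26 df and 6.2% at 24 df.

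**Step 3: add the sandwich bias.** With equal villages and equal leverages, the expected sandwich variance is the true variance times (1 - p/30) x 30/29 = (30 - p)/29. The standard error is low by the square root of this, and the effective critical value is 1.96 times that root. The interval width needed is the t quantile divided by the effective critical value.

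| p | (30-p)/29 | root | 1.96 x root | type I error | width needed |
|---|---|---|---|---|---|
| 2 | 0.966 | 0.983 | 1.926 | 6.4% | 2.048/1.926 = 1.06 |
| 4 | 0.897 | 0.947 | 1.856 | 7.5% | 2.056/1.856 = 1.11 |
| 6 | 0.828 | 0.910 | 1.783 | 8.7% | 2.064/1.783 = 1.16 |

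**Step 4: simulation under no effect.** Stratified allocation of 30 villages. The Poisson cells used 2,000 runs each; the Monte Carlo standard error is about 0.6 points. Ranges are over the scenarios tried.

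| Test | no strata covariates | river + linear size | river + quartiles |
|---|---|---|---|
| Mixed Poisson, robust, z (20-24 mothers, ICC 0.04 and 0.1) | 5.5-6.6% | 7.3-8.4% | 7.8-9.1% |
| Mixed Poisson, robust, z (about 26 mothers, ICC 0.04) | not run | 6.8-7.9% | 8.3-9.3% |
| Mixed linear, robust, z (two sets) | 6.1-6.9% | 7.1-7.9% | 7.7-10.2% |
| Mixed Poisson, model-based, z | 5.9-7.1% | 7.6-8.8% | 7.3-9.2% |
| Mixed Poisson, robust, t on 30-p df, sandwich uncorrected | 4.6-5.4% | 6.1-7.1% | 6.7-7.5% |
| Village log rates, t on 30-p df | 4.5-5.2% | 4.9-5.7% | 3.9-4.7% |

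In the linear case, a bias-corrected sandwich with a t reference, or a village-level t test, gave about 4.5-6.1%.

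The hand calculation and the simulations agree. With the strata covariates in the model, a t reference alone is not enough.

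**Step 5: does the planned effect survive?** With 11.3% against 36.3%, 12 mothers per village and ICC 0.04:

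- Design effect = 1 + ((0.22² + 1) x 12 - 1) x 0.04 = 1.463.
- Effective n per arm = 180/1.463 = 123.0.
- Standard error = sqrt((0.113 x 0.887 + 0.363 x 0.637)/123.0) = 0.0519, so effect/SE = 0.25/0.0519 = 4.82.
- Power from a noncentral t is 99.6% at 24, 26 or 28 df.

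This exceeds the 95% stated in section 1.2.6. That mismatch is a separate matter and does not affect the type I error.

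**The case against.** The strongest reply is that the point rests on silence. Section 1.2.11 names neither z nor t, and degrees of freedom and sandwich corrections are often left to a statistical analysis plan, which may exist here. A reader might infer that the protocol prescribes a normal reference or rules out a correction. It does neither; the z reference is the usual default and is assumed. What the protocol does fix is the variance estimator, the village-level covariates and the 5% level for 30 villages, and section 2.1.5 makes that the 2-year plan. Run in the usual way, this does not deliver its level.

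A second reply is that robust errors are not to blame. A reader might infer that deleting that sentence would cure the problem. It would not: model-based errors with z were inflated to about the same extent. The stated reason for robust errors is also sound, since a Poisson model is applied to binary outcomes and to counts bounded by opportunities. The sandwich should therefore be corrected, not dropped, for the Poisson models.

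Third, the size is conditional. Section 1.2.11 does not say whether village size enters linearly or as quartiles, several simulation inputs are assumed, and the baseline covariate was not simulated. This stands, and is why a range is given.

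Finally, a reader might infer that borderline 2-year results are likely. The documents do not support this. The introduction to section 2 speaks of any residual effect, and section 2.1.2.2 reports pilot-village signs that the behaviours persist.

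**Conclusion.** The point holds in conditional form. With 30 villages, uncorrected robust errors and an assumed normal reference, nominal 5% tests run at about 7-8% with linear village size and about 8-10% with quartiles. Without strata covariates the figure is about 5.5-7%, but the primary analysis includes them. Nominal 95% intervals then cover about 90-93%, and by the hand calculation should be about 11% wider (linear size) or 16% wider (quartiles).

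The inflation is modest. It could change the reading of a borderline result, but it would not overturn an effect of the planned 25 points. It is not evidence that any particular result is wrong. The absolute figures depend on the assumed z reference and on how village size is entered; the direction was the same in every scenario tried.

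**What to change.** In section 1.2.11, and so for the 2-year data under section 2.1.5:

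- **Poisson models (primary and binary outcomes).** Keep the mixed Poisson rate ratio or relative risk as the estimate. Base tests and intervals on a bias-corrected cluster sandwich with a t reference on 30 minus the number of village-level parameters (about 24-26).
- **Acceptable alternative.** Use a village-level analysis of log rates with the same t reference, or a permutation test within the randomisation strata. The log scale keeps the ratio measures chosen in section 1.2.12, which a regression of raw village rates would lose. State how villages with no events are handled; the check above added 0.5 to numerator and denominator.
- **Continuous outcomes.** Use REML with Kenward-Roger in place of robust errors.
- **Village size.** State whether it enters linearly or as quartiles, since this fixes the degrees of freedom.

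The cost is slightly wider intervals, a few sentences and a few lines of code. No new data are needed, and power for the planned effect stays above 99% at ICC 0.04 with the t reference.

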### **Corresponding author:**

[name], Clinical Senior Lecturer, Institute of Applied Health Research, College of Medical and Dental Sciences, University of Birmingham, [name]

[[contact]](mailto:[contact]), (registered on BMJ site as [contact])

[contact]; [contact]

**Summary of 2-year follow-up protocol:** The Gambia has high rates of under-5 death from diarrhoea and pneumonia that peak during the weaning age. Community-based interventions may reduce weaning-food contamination and disease rates. A clustered randomised controlled trial was conducted in the Central River Region of the Gambia in 2012-15 to trial a community level weaning-food safety and hygiene intervention.

The initial registered protocol outlined a 6-month follow-up. A random sample of 30 villages (clusters) with a population of 200–450 was selected and after a baseline survey clusters were randomly assigned using a random number table within strata 1:1 to either – four intensive days of a community level campaign like intervention to improve weaning-food hygiene practices plus a reminder visit at 5 months, delivered through traditional Gambian performing arts and the existing public health and village structures – or to a one day community intervention campaign for use of water in domestic gardening in the control arm. The primary outcome was a composite score of five key food-related hygiene behaviours (observed), hereafter called 5-behaviours. Secondary outcomes included microbiological contamination of food and water for child's consumption; the prevalence of diarrhoea and respiratory diseases; and mothers' reporting of diarrhoea admission. Outcomes were measured at 6 months after the intervention in a cross-sectional survey of 20 randomly selected mothers with a child aged 6–24 months per village. Outcomes were compared in an intention-to-treat analysis between intervention and control group adjusted for mother's age, mother's education, sex of the index child, and number of children in the household.

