Further funds were secured to follow-up to assess the ongoing effect of the intervention 2 years after the 5th month reminder visit. There have been no further contact with the villages after the 6-month follow-up. Methods will be similar to the 6-month follow-up. Outcomes will be measured in a cross-sectional survey of 26 randomly selected mothers with a child aged 6 to 36 months per village. The same primary and secondary outcomes measured in the

6-month follow-up will be measured at 2 years with the addition of assessing the effect of the intervention on hospitalisation from acute respiratory tract infections (ARI) and health economics analysis of ARI for the child, family-food behaviour and diarrhoea outcomes, qualitative studies. There will also be two nested cross-sectional studies examining the degree of agreement between two methods of measuring microbiological water quality and the play and care-giving behaviours related to contamination of toddler's hands outside in the yard.

**Trial registration:** The trial was registered on the 17th October 2014 with the Pan African Clinical Trial Registry in South Africa with number PACTR201410000859336.

**Keywords:** cluster randomised controlled trial, diarrhoea, pneumonia, behaviour change, weaning-food, hygiene, food preparation, community intervention, performing arts, dramatic arts, motivational drives, scalability, Africa.

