## **1.2 Methods:**

### **1.2.1 Design, setting and population**

The cRCT was conducted in the Central River Region (CRR), one of the seven administrative regions in the Gambia with a total of 659 villages, and a population of 201,506 of which 41,334 (20%) are under-5 years olds. CRR was selected as it has the highest incidence of diarrhoea in the Gambia, particularly in children aged 6–24 months (26.5% of children under-5 had diarrhoea in the two weeks preceding the UNICEF Multiple Indicator Cluster Survey (MICS) in 2010, verses 17% nationally. The rates for ARI of children under-5 were 14.2% in CRR compared to 6% nationally). As with other regions, UNICEF and the Ministry of Health and Social Welfare (MOH) have selected a number of villages (158 in CRR) to become Primary Health Care villages where they have trained (for four weeks) a Village Health Worker (VHW) and a Traditional Birth Attendant (TBA) to provide health promotion and basic health support to the villagers.

Inclusion criteria for study villages were Primary Health Care villages with a population of 200–450 within CRR. Exclusions for the villages were those that were within 5km of already selected villages.

Inclusion criteria for households within the selected villages for baseline were mothers with children aged 6-24 months expecting to be resident in the village for the following six months. There were no other exclusions. Inclusion criteria for households for the evaluation of the intervention were mothers with children aged 6-24 months at the time of the four day visit of the intervention team to their village. Exclusions were the unavailability of the index child's main carer for cooking the index child's weaning-food during the evaluation visit.

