### **2.1.3 The population sample of mothers per village for 2 years evaluation data**

**(including additional variables in 2.1.1 and 2.1.2)**

We aim to select mothers who are currently weaning or have children who may have a combination of weaning and family food (E.g. 24-36month old children). As such some will be those who would not have been pregnant or had an infant at the time of the 4-days campaign visits or the 5th-month reminder.

For sampling frame, as with the 6-month follow-up the baseline list of children in the villages will be updated using the maternal-child health register and village health worker's list of children in each village. From these there will be 26 mothers chosen from each of the control and intervention villages. Sample size will be 23-26 mothers per cluster (as suppose to the target of 20 at the 6-month follow-up) because as indicated in the 6-month sample size calculation a minimum of 12 mothers per cluster of weaning children is needed (see above sample size for 6-month follow-up) but at 2 years we have 2 groups of mothers: new mothers and those who are mothers at the time of the 4-days campaign activities. (New mothers at 2-year follow-up are those with children 6-25month who will be eating weaning-food. Children aged 26-36 months will still, for the most part, be eating weaning-food at 2-year follow-up plus some of the family-food. Their mothers would have been pregnant during the 4-days campaign visits of the intervention in December to February 2014 and ready to wean at the 5th-month reminder visit. This population are the candidates most likely to *remember and practice* the hygienic behaviours while still *making* weaning-food during the 2-year assessment.) Therefore, we aim to have approximately 12 of each sub-group of mothers recruited. All individual mothers or main carers of children 6 to 36 months living in the village for a minimum of 2 years will be eligible for selection but mothers who are not available for cooking the child's weaning-food during the 2-year evaluation visit will be

excluded. (All mothers were available for the 6-month evaluation survey so we envisage very few or no mothers will be excluded).

To capture all these sub-groups of mothers, the selection of the mothers will be stratified as follows:

1. All mothers of children age 18 to 24 months will be chosen.
2. The rest of the mothers will be chosen according to the following formula:

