$$x = \frac{(26 - \text{all mothers with 18 to 24 month old children})}{2}$$
3. Then,  $x$  number of mothers with children aged 6-18 months and  $x$  number of mothers with children aged 24-36 months will be randomly chosen from the list.

For sub-group analysis, ‘New mothers’ will be classified as those with children 6-25m since these mothers would not have had a child at before the 5th village reminder visit and the 6-month evaluation and so as mothers were not a part of the MaaChampion program when any part of the intervention was taking place in the villages.

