### **2.1.5 Statistical analysis for 2 years evaluation data (including additional variables in 2.1.1 and 2.1.2)**

The statistical analysis plan for the analysis of the 2-year follow-up evaluation data will follow the same analysis plan described earlier for the 6-month follow-up evaluation data.

Sub-group analysis will be performed to establish the effect on the ‘new mothers’.

All analyses will be conducted using Stata 15.

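### The 2-year sample is selected by child age, but the carried-over adjusted model omits child age; the arm comparison is not biased, and adding the covariate is nearly free

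*Protocol*

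**What the plan says.** Protocol section 2.1.3 sets the 2-year selection rule. "All mothers of children age 18 to 24 months will be chosen"; the places left out of 26 are halved to give x. Then x mothers are drawn at random from those with children of 6–18 months, and x "number of mothers with children aged 24-36 months will be randomly chosen from the list". The Summary describes the result as "26 randomly selected mothers with a child aged 6 to 36 months per village". The 6-month evaluation covered 6–24 months only (section 1.2.1).

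Section 2.1.5 says the 2-year analysis "will follow the same analysis plan described earlier for the 6-month follow-up evaluation data" and adds only the 'new mothers' sub-group, which section 2.1.3 defines by a child of 6–25 months.

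In section 1.2.11, "the primary analysis will be unadjusted for all covariates other than cluster and those covariates used in the stratified randomisation procedure", namely side of the river and village size. The secondary analysis adds a pre-specified set: "age and education of mother, parity, sex of child, order of intervention implementation", and intermediate outcomes where health outcomes are concerned. The Summary describes the 6-month comparison as "adjusted for mother's age, mother's education, sex of the index child, and number of children in the household". Neither list contains the child's age, and no sampling weight or age-stratum term is given.

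The protocol itself links outcome to age. Section 1.2.1 says the region was chosen because "it has the highest incidence of diarrhoea in the Gambia, particularly in children aged" 6–24 months. Section 2.1.3 expects mothers of 26–36 month olds to be the likeliest to recall and still practise the behaviours.

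**The concern.** The covariate list was written for a survey of a narrower age range without age strata. It is carried unchanged to a survey in which child age decides who is sampled and the range runs to 36 months. Child age is thus both a design variable and, by the protocol's own account, a predictor of illness, yet no covariate list contains it.

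Two things are at stake. The adjusted model leaves age-related variation in the residual, which costs precision. And where the sampling fractions differ by age, the pooled effect refers to the sample's age mix, not the village's, so the two can diverge if the effect differs by age.

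This is more than detail left for a later analysis plan: section 1.2.11 names its adjusted set as pre-specified, and section 2.1.5 applies it to the new design. The provision to use baseline data as a covariate does not fill the gap, because the 2-year survey is a fresh cross-section.

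**Working it through.** The protocol gives no figure on this point to reproduce; the power statement in section 1.2.6 does not depend on it.

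**Inputs from the protocol.** Village population 200–450; under-5s 41,334/201,506 = 20.5% of the regional population (both section 1.2.1); the selection rule in section 2.1.3; 15 villages per arm.

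**Assumptions.** Every village has the regional under-5 share, ages are uniform over the 60 months, and each mother has one eligible child.

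**1. Sampling fractions.** Expected children of 18–24 months: a = 0.2051 × population × 6/60. In each of the other two strata: b = 0.2051 × population × 12/60. Then x = (26 − a)/2, and the fraction in each outer stratum is min(1, x/b). Among eligible children, 18–24 months makes up 6/30 = 20%.

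| Population | a | b | x | Fraction, outer strata | 18–24 months, share of sample |
|---|---|---|---|---|---|
| 200 | 4.1 | 8.2 | 10.95 | 1.00 | 20% |
| 250 | 5.1 | 10.3 | 10.44 | 1.00 | 20% |
| 325 | 6.7 | 13.3 | 9.67 | 0.73 | 25.6% |
| 400 | 8.2 | 16.4 | 8.90 | 0.54 | 31.6% |
| 450 | 9.2 | 18.5 | 8.39 | 0.45 | 35.5% |

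The fraction for 18–24 months is 1.00 throughout.

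**2. Share of 'new mothers' (6–25 months).** Eligible children: 19/30 = 63%. Sample: (x + a + x/12)/26, which is 17.1/26 = 66% at 325 and 18.3/26 = 70% at 450. At 250 or below everyone is taken and there is no difference.

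**3. Chance imbalance between arms.** Treating a as Poisson with mean 6.7, the SD of the between-arm difference in the 18–24 month share is √(2 × 6.7/15)/26 = 3.6 points. Because x is equal in the younger and older strata, extra 18–24 month olds displace both equally. With assumed diarrhoea prevalences of 30/25/15% (6–18/18–24/24–36 months), the middle stratum differs from the mean of the other two by 25 − 22.5 = 2.5 points. One SD therefore shifts the contrast by 0.036 × 2.5 = 0.09 percentage points. Prevalences of 35/25/10% give the same result.

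**4. Pooled effect.** Pooled risk ratio = Σ(w·p·r)/Σ(w·p), where w is the sample mix (unweighted) or the village mix (weighted), p is the assumed control prevalence (30/25/15%) and r is the assumed age-specific ratio.

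| Assumed pattern of r | 325, unweighted / weighted | 450, unweighted / weighted |
|---|---|---|
| 0.7 at every age | 0.700 / 0.700 | 0.700 / 0.700 |
| 0.9 new, 0.6 exposed | 0.834 / 0.828 | 0.843 / 0.828 |
| 0.9 / 0.4 / 0.9 by stratum | 0.762 / 0.791 | 0.710 / 0.791 |

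In the second row the 24–36 month stratum gets 0.9 × 1/12 + 0.6 × 11/12 = 0.625, because one month of it falls in the 'new' group.

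**5. Precision.** Variance in diarrhoea explained by age stratum = Σw(p − m)²/[m(1 − m)] with w = 0.4/0.2/0.4 and m = 0.23. This is 2.6% for 30/25/15% and 7.1% for 35/25/10%.

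**6. Cost of weighting.** The Kish factor n·Σw²/(Σw)², with w now the sampling weight, is 1.00 at 250 or below, 1.02 at 325 and 1.11 at 450.

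**The case against.** The strongest reply is that nothing here threatens the trial's contrast. A reader might infer that leaving child age out of the models biases the comparison of arms. The protocol does not support that: section 2.1.3 applies one rule in both arms, the expected fractions vary with village size, section 1.2.9 stratifies randomisation by population quartile, and section 1.2.11 already puts village size in the primary model. A reader might also infer that chance age imbalance is a real danger; step 3 shows it is trivial. Equal numbers from the outer strata protect the young–old balance wherever both strata can supply x. In the smallest villages everyone is taken, so there is no unequal sampling there.

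It is also fair to say that:

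- Child age is not wholly absent from the analysis, since it defines the 'new mothers' sub-group.
- The illness argument concerns secondary outcomes.
- A primary model limited to clustering and the randomisation strata is a standard choice that keeps the 2-year result comparable with the 6-month one.
- The protocol never claims to estimate a village-average effect.

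All of that stands, and it removes any case for changing the primary model. It does not answer the narrower point. The sub-group analysis does not account for the sampling, because its 25-month cut crosses the 24–36 month stratum. And an adjusted model that includes mother's age and child's sex but leaves out the variable used to draw the sample is hard to justify.

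**Conclusion.** The point holds as a modest, worthwhile improvement to the adjusted 2-year analysis. It is not an error that invalidates a result.

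- **Bias in the arm comparison:** none from this source.
- **Precision:** some is forgone, mainly for the illness outcomes, where age stratum would explain roughly 3–7% of the variance in diarrhoea under the assumed prevalences.
- **Meaning of the pooled effect:** in larger villages it leans towards 18–24 month olds. If the effect is the same at every age, nothing changes. If it differs between new and exposed mothers, the split the protocol itself has in mind, the risk ratio moves by about 0.00–0.015 under the ratios assumed. The 0.08 shift in the last row of step 4 needs an effect peculiar to 18–24 months, which nothing in the protocol suggests.

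The sampling shares rest on the three assumptions stated in the working. The prevalences and age-specific ratios are illustrative and are not in the protocol.

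**What to change.** In section 2.1.5, state that for the 2-year outcomes:

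1. The pre-specified adjusted model also includes child age, either as the three sampling strata or as months in a smooth term.
2. One sensitivity analysis weights each mother by the inverse of the village-by-age sampling fraction. This is needed as well as the covariate, because a covariate alone does not restore the village age mix if the effect varies with age.
3. The strata in section 2.1.3 do not overlap; at present 18 and 24 months each fall in two of them.

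The Summary should describe the sample as stratified by child age. The primary model can stay as written.

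The cost is two extra parameters if the strata are used, and a variance inflation of about 0–11% in the weighted analysis only. Child age is already recorded in order to draw the sample. The number of eligible mothers listed in each village and stratum must be kept so that the weights can be formed.
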